## Abstract

**Background:**

Upper crossed syndrome (UCS) refers to specific altered muscle activation and changed movement patterns along with some postural deviations in the upper quarter of the body. This syndrome might contribute to the dysfunction of the cervicothoracic and glenohumeral joints.

**Objectives:**

The present study will aim to investigate the effectiveness of a comprehensive corrective exercises program (CCEP) and subsequent detraining on alignment, muscle activation and movement pattern in men with UCS.

**Methods/design:**

This is a parallel-group randomized controlled trial. Participants will be 22 men aged 18 to 28 years who are suffering from UCS. Participants in the intervention group will conduct CCEP (three times a week for 8 weeks), followed by 4 weeks of detraining. The control group will do their daily activities. Participants will be randomized (1:1) into the intervention or the control group. The primary outcome will be upper trapezius activations. Secondary outcomes consist of electromyography of middle and lower trapezius and serratus anterior muscles, scapular dyskinesis test, forward head and shoulder angles, thoracic kyphosis angle, and neck flexion pattern test.

**Discussion:**

We propose to evaluate the effectiveness of a randomized controlled trial of a CCEP in men with UCS on their alignment, selected muscle activations, and relevant movement patterns. Results from our trial may provide new insights into the effects of exercise not only on the alignment but also on muscle activation and movement patterns that are important outcomes for people with postural malalignments and, if successful, could assist therapists in evidence-based clinical decision-making.

**Trial registration:**

Iranian Registry of Clinical Trials, IRCT20181004041232N1. Registered on 26 October 2018.

## Background

Most people will see a medical practitioner or another health care provider at least once in their lifetime because of neck, shoulder and back pain [1, 2]. At a societal level, these pains are also responsible for substantial costs, including healthcare expenditure, disability insurance, and work absenteeism [3]. Previous studies showed that these pains might be associated with abnormal alignments [4, 5]. One of these malalignments is the upper crossed syndrome (UCS), which was defined as a muscular imbalance pattern by Vladimir Janda MD (1923–2002) [6]. UCS refers to specific altered muscle activation and movement patterns along with some postural deviations [7]. Alterations in muscle activation include overactivity of the upper trapezius, levator scapula, and pectorals muscles and underactivity of the deep cervical flexors, middle and lower trapezius, and serratus anterior [8]. Due to kinetic and muscular chains, there are altered scapular movement patterns (scapular dyskinesis) and specific postural changes, including forward head and shoulder posture and increased thoracic kyphosis [7, 9]. These changes can lead to reduction in the stability of the glenohumeral joint and to various musculoskeletal symptoms in the head, neck, and shoulder [7, 8, 10].

Over recent decades, therapists have been seeking to design appropriate exercises to correct musculoskeletal malalignments mainly through structural and functional approaches [11–13]. In the traditional structural approach, the changes observed in malalignments such as in UCS are attributed to biomechanics and are presumed to lead to adjustments in the length and strength of local muscles [11, 14]. This may account for the stretching of short muscles and strengthening of weakened muscles at the site of the problem in the correction phase, while ignoring other related malalignments [14]. Interestingly, despite the popularity of this method, very little research has been conducted based on this theory [15]. Furthermore, some review studies have questioned the effectiveness of strengthening and stretching exercises to improve postural disorders [16, 17].

In contrast, the functional (neurological) approach to musculoskeletal problems is based on the interaction of the central and peripheral nervous systems, and the involvement of the muscular and skeletal structures in producing and controlling motion [6, 18, 19]. In this functional approach, the musculoskeletal problems are attributed to the role of muscles in motor function; furthermore, changes in the alignment result not only from changes in muscle length and strength but also from more important changes in muscle neuromuscular factors, such as muscle recruitments [13, 20]. In fact, the motor control unit may change the muscle activation strategy for temporary stabilization due to the presence of dysfunction. These changes in motor recruitment will alter the muscular balance, movement patterns, and eventually the motor program [12]. Similarly, Hodges et al. noted that motor control interventions require tailoring to each individual’s posture, muscle activation, and movement pattern [21]. However, this theory has not been tested in practice for the prevention and treatment of musculoskeletal malalignments.

Hence, for the assessment of UCS, the alignment and its side effects are often evaluated, such as increase in thoracic kyphosis or forward head angles, while less attention has been paid to the keystone, i.e., the scapulae, and the relevant altered muscle activation and movement patterns [22]. In this regard, many researchers and therapists have only evaluated one of the affected regions, such as head, shoulders, or spine, separately and reported a degree of postural deviation regardless of other relevant malalignments and patterns of the muscle activation and related movement patterns, such as scapulohumeral rhythm or neck flexion [23–25]. In addition, the design and implementation of the training protocol are based on the traditional structural approach, in which stretching exercises for short muscles and strengthening exercises for weak muscles are prescribed at the site of malalignment [22, 24], while the neuromuscular factors and related movement patterns may not be considered. To the best of our knowledge, no studies identifying and correcting UCS have considered the three components of alignment, movement pattern, and muscle activity in both assessment and correction processes.

### Study objectives

The primary aim of the present study is to evaluate the effectiveness of a comprehensive corrective exercise program (CCEP) in young men with UCS for 8 weeks, as measured by alignment (position of the scapula, head and neck, shoulder, and thoracic spine), electromyography activity of selected muscles (upper, middle and lower trapezius, serratus anterior), and specific movement patterns (scapulohumeral rhythm and neck flexion). A secondary aim is to evaluate the effects of the program after 4 weeks of detraining after the intervention.

## Methods/design

### Study design

This is a parallel-group randomized controlled trial comparing an intervention group receiving an 8-week CCEP followed by 4 weeks of detraining to a control group who will only do their daily activities. The study will be performed at the Laboratory of Health and Sports Medicine Department, University of Tehran, Tehran, Iran. Initially, participants will take part in the baseline assessment process. They will then receive the intervention for 8 weeks. After the end of the intervention phase, all the measurements will be repeated. Finally, a follow-up assessment will be performed after a 4-week detraining period. The study schedule is presented in Table 1 and a flow diagram is shown in Fig. 1. The study protocol is reported in accordance with the SPIRIT guideline.

**Table 1 Tab1:**
[figure not shown]
Schedule of the study

**Fig. 1 Fig1:**
[figure not shown]
Study flowchart

### Ethical aspects

Before starting the project, all participants will be asked to complete and sign an informed consent form. Ethics approval was obtained on August 28, 2017, from the Ethics Committee on Research at University of Tehran, Iran (IR.UT.REC.1395026). The protocol was approved at the Iranian Registry of Clinical Trials on 2018-10-26 (IRCT20181004041232N1).

### Study participants and eligibility criteria

The participants consist of 24 men with UCS aged 18 to 28 years. They will be recruited from the students of the University of Tehran, Iran, through advertisements on bulletin boards. They will be screened primarily by observation for three main factors related to UCS, including altered alignment, muscle activation, and movement patterns. Since the scapulae are the keystone in UCS, participants who have any abnormality in the position and rhythm of the scapula, as measured by the scapular dyskinesis test, will be recruited. In addition, they will be assessed for presenting any postural changes such as forward head (≥ 44°), round shoulder (≥ 49°), or excessive thoracic kyphosis (≥ 42°) as measured by photogrammetry and flexicurve, respectively [15]. Also, to ensure any change in muscle activation is related to postural changes, some confirmatory tests, including muscle length tests for upper trapezius and pectoral muscles as well as muscle strength tests for middle and lower trapezius and deep cervical flexor, will be used. Individuals will be excluded from the research process if they do extra physical activity and sports that may affect the outcomes of the research, have any visible malalignment in the pelvis and lower extremities, have a history of fracture, surgery, or joint diseases in the spine, shoulder and pelvis, have a rotation greater than 5° on the forward bending test because of scoliosis [15], or have a bodyweight outside the normal range (body mass index between 18 and 25) [23].

### Randomization

Participants will be randomized using computer-generated block randomization in a 1:1 ratio, followed by a concealed allocation through opening sequentially numbered, opaque and sealed envelopes; a card inside will indicate the group into which the participant will randomly be allocated, i.e., the intervention or the control group. Participants can discontinue the project at any time. However, all efforts will be made to avoid missing data. The specific way to deal with missing data will be determined at a data review meeting before starting statistical analyses.

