### Outcome measures

All outcome measurements will be performed by the main researcher at baseline, 8 weeks (after intervention), and 12 weeks (follow-up). Demographic information (i.e., sex, age, body mass index) will be measured before the intervention.

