### Sample size

The sample size was calculated using the G*Power software (G*Power, version 3.0.10, Germany). It was based on a pilot test of seven participants, and on the assumption that a 10% difference in muscle activity [34] and an 11° difference in kyphosis angle [41] between groups would constitute clinically meaningful differences. It was calculated that a sample consisting of at least 18 participants would suffice to obtain 80% power with d = 0.80 effect size, and a confidence interval of 0.95. It should be noted that the effect size was reported in the previous study which compared scapular muscle activity between the interventions and control groups. Effect sizes ranged from 0.6 to 0.9 for the EMG amplitude and onset [42]. Since a few participants may drop out of the intervention studies, we will include 24 (assuming a drop-out rate of approximately 25%).

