### Statistical method and analysis

Assessments of statistical procedures will be performed using IBM SPSS version 20 for Windows (SPSS Inc., Chicago, IL, USA). All variables will be reported using the descriptive statistic (mean, standard deviation). Shapiro-Wilk test will be used to assess the normality of data. Repeated measures ANOVA will be used to compare the means. If mean difference is significant, then the Bonferroni-adjusted post-hoc test will be calculated. The independent *t*-test will also be used for comparison between groups. Finally, the effect size will be calculated for the magnitude of the difference using the Cohen method. The significance level will be set at *p* < 0.05.

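### The missing-data rule is left to a pre-analysis meeting not stated to be masked to arm, and by default the planned repeated-measures ANOVA excludes any man who misses one visit

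*Protocol article*

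**What the plan says.** The Randomization section allows men to leave the project at any time and promises efforts to avoid missing data. It then says: "The specific way to deal with missing data will be determined at a data review meeting before starting statistical analyses". It does not say who attends the meeting or whether they see arm labels.

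Under Statistical method and analysis, the work is to be done "using IBM SPSS version 20 for Windows", and "Repeated measures ANOVA will be used to compare the means". Bonferroni-adjusted post-hoc tests follow a significant result. Independent t-tests are also planned between groups, with no time point given. No treatment of incomplete series is described.

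Under Outcome measures, the main researcher takes all measurements at baseline, week 8 and week 12. Under Study objectives, the 8-week effect is the primary aim and the effect after detraining is secondary. The Discussion lists the lack of a double-blind design as a limitation.

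Under Sample size, the plan needs 18 men and states "we will include 24 (assuming a drop-out rate of approximately 25" per cent. Under Trial status, ten men had been included and recruitment was still open.

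**The concern.** Two features combine. First, the protocol does more than stay silent on missing data. It assigns the choice to a meeting just before analysis, by which time the measurements will presumably be in. Nothing stated prevents those present from knowing both allocation and results, so the method could be chosen, knowingly or not, because of what it does to the result.

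Second, the named analysis makes that choice matter. Classical repeated-measures ANOVA uses only men with a value at every visit. If the meeting decides against imputation, the main multi-visit analysis covers completers only, and absence from the secondary week-12 visit removes a man from the ANOVA assessment of the primary 8-week aim. The arms also carry unequal burdens: three supervised sessions a week for 8 weeks (3 × 8 = 24 sessions) against ordinary daily activities. Drop-out that differs by arm or depends on response is plausible, though no figure in the document shows it.

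**Working it through.** **Inputs.** From Sample size: 18 men needed, about 25% drop-out, 24 enrolled. From Outcome measures: three visits, two of them after baseline. From Randomization: 1:1 allocation, so 12 per arm. The Abstract gives 22 men instead of 24; that is a separate inconsistency and is not used here.

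**The plan's own figure.** Enrolment = needed / (1 − drop-out) = 18 / (1 − 0.25) = 24. This reproduces. The loss allowed for is 24 × 0.25 = 6 men, leaving 18.

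**Which analysis keeps which man (baseline present, nothing imputed).**
- Weeks 8 and 12 both observed: kept by the ANOVA, by a week-8 t-test and by a mixed model.
- Week 8 only: excluded from the ANOVA and its post-hoc tests; usable in a week-8 t-test; kept by a mixed model.
- Week 12 only: excluded from the ANOVA and from a week-8 t-test; kept by a mixed model through his week-12 value.
- Neither: excluded from the ANOVA and t-tests. A mixed model with baseline as covariate has no outcome from him either.

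**How quickly single missed visits add up.** Assume each post-baseline visit is missed independently with probability p (the document gives no such rate). The share of men who are incomplete is 1 − (1 − p)².
- p = 5%: 1 − 0.95² = 9.75%, or 24 × 0.0975 = 2.3 men.
- p = 10%: 1 − 0.90² = 19.0%, or 4.6 men.
- p = 15%: 1 − 0.85² = 27.75%, or 6.7 men.

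Modest visit-level absence can therefore exclude about as many men as the 25% allowance.

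**Can the bias be sized?** Only by assumption. Suppose 3 of the 12 exercise-arm men drop out, the 9 completers gain 0.8 SD, and control drop-outs resemble control completers. If the 3 gained nothing, the as-randomised effect is (9 × 0.8 + 3 × 0) / 12 = 0.6 SD, and the completer estimate is 0.8 / 0.6 = 1.33 times too large. If they gained as much as the completers, it is (9 × 0.8 + 3 × 0.8) / 12 = 0.8 SD and there is no bias. The document does not say where in that range, or outside it, the trial would fall.

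**The case against.** Several counter-arguments have force.

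- **The protocol never says that incomplete cases will be deleted.** This stands. Deletion is the method's default, and the meeting might choose imputation. The point is therefore conditional. A reader might infer that the completer analysis is already decided; the text does not go that far.
- **The t-tests could keep a man at week 8.** This also stands. A reader might infer that drop-outs vanish from every comparison, but that is true only of men with no post-baseline value.
- **Lack of blinding is inferred.** The Discussion says only that the trial is not double-blind. It does not rule out a masked assessor or a masked review, and a corrective exercise specialist, not stated to be the measurer, supervises the sessions. The fair statement is that no masking is described.
- **The loss is already budgeted.** Correct: 24 are enrolled so that 18 remain. The concern is bias and late choice of method, not an unplanned shortfall.
- **Missing-data detail usually sits in an analysis plan.** It does, and the meeting precedes the analyses. But the protocol itself says how the choice will be made, and without stated masking that is a rule fixed badly rather than detail left out.
- **A mixed model would not cure the 0.8 versus 0.6 SD example.** Correct. With no post-baseline values from the 3 men, it would still estimate about 0.8 SD. Only following those men, or a sensitivity analysis, addresses that case.

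A reader might also expect a power gain. For a two-sided t-test at d = 0.80, power is 35.8% with 9 per arm and 46.6% with 12, but the higher figure needs outcomes on all 24 men, which the change of model cannot supply.

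**Conclusion.** The concern holds in a limited, conditional form. The missing-data method is to be chosen just before analysis at a meeting not stated to be masked. Unless values are imputed, the ANOVA and its post-hoc tests exclude every man missing any of the three visits, including men who have the week-8 value that the primary aim needs. The plan's own allowance puts the scale at about 6 of 24 men, a planning figure and not a forecast.

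This rests on two readings: that a data review meeting before analysis takes place once data are collected, and that repeated-measures ANOVA is run in its classical form. The size of any bias cannot be derived from the document. The point should be corrected because a better method is available at little cost; it does not show that the trial's result will be wrong.

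**What to change.** State the rule now, while recruitment is open:

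- Analyse all randomised men in their assigned arm.
- For the continuous outcomes, replace repeated-measures ANOVA with a likelihood-based mixed model: baseline as covariate, with group, visit and group-by-visit terms. SPSS offers this in its MIXED procedure. Name the week-8 group contrast as primary. The model uses every observed week-8 or week-12 value.
- Invite men who stop exercising to the week-8 and week-12 assessments already scheduled.
- Add one conservative sensitivity analysis for men with no post-baseline data, since the mixed model does not recover them. Control-based multiple imputation is one option; filling in a single control mean would understate the variance.
- Hold the data review meeting with arm labels masked.

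The cost is a different procedure in the same software, one extra analysis, and reliance on a missing-at-random assumption for the main model, which the sensitivity analysis is there to test. No specific gain in power should be claimed.

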### Comprehensive approach

The comprehensive approach (Fig. 2), which is a new approach to corrective exercises [15], takes advantage of the strengths and weaknesses of traditional approaches to achieve the best outcome in correcting musculoskeletal malalignments. It was initiated in 2014 by Seidi et al., who compared the efficacy of comprehensive and traditional corrective exercise programs on the kyphosis angle [15]. The general purpose of this approach is to pay attention to alignment, muscle activation, and movement pattern simultaneously across the whole body rather than at just a single site during both the assessment and correction phases.

**Fig. 2 Fig2:**
[figure not shown]
Comprehensive approach flowchart

#### Intervention

An 8-week CCEP will be structured to include three phases. In the initial phase of the exercise program, the participants will become cognizant of the purpose and the quality of the exercises. This is characterized as voluntary control of exercise, requiring cortical regulation of movement and a lot of concentration on the part of the participants [12]. Participants will be asked to focus only on the scapular muscles, i.e., an internal focus [26] while their alignment is corrected passively. So, the exercises will be executed in non-weight bearing positions and the participants only try to contract underactive muscles isometrically and relax overactive muscles around the scapula for normalization of scapular position and motion [27, 28]. The participants will be instructed to reproduce this orientation of scapula actively using auditory (from therapist) and kinesthetic cues such as palpation [28]. Once a participant regains sufficient control over scapular muscles, he will focus externally on it and turn the internal focus of attention to correcting proximal segments through chin tuck, retraction of shoulders, and straightening the upper thoracic spine [29]. Then, he will do the exercises in different weight-bearing positions, and after restoring muscle balance in the static conditions, he will try to add upper extremity movements in various training positions. Also, the respiratory pattern of participants will be controlled during this phase and necessary feedback will be provided [13]. Since the quality of exercises is highly important in this phase, the participants should not feel fatigued while doing the exercises because fatigue may alter optimal muscle activations and movement patterns [30].

Once the participants can contract the appropriate muscles in a correct alignment during the best movement pattern, they should be able to maintain this for a long time. This goal will be addressed in the improvement phase when necessary tissue adaptations occur by increasing the load of exercises [31, 32]. Placing the participants in weight-bearing positions and using some tools such as training balls and Thera-Bands will reinforce their abilities gradually. During this phase, the participants will only focus on the goal of exercises (external focus) [29]. Moreover, because UCS is representative of underlying potential sensorimotor dysfunction, some functional balance exercises will be included [12]. The frequency and intensity of the exercises will increase progressively during the study, provided that participants can demonstrate good-quality movement. In the final phase, i.e., the maintenance phase, the participants will try to maintain the training adaptations [32]. All exercises will be performed under the supervision of a corrective exercise specialist. The participants will not conduct any extra exercises at home. However, they will be asked to avoid sustaining poor posture. More details about the intervention protocol are presented in Appendix 1. The control group will be asked to do their ordinary daily activities and not to participate in any exercise programs. After the study is completed, the control group will undergo the exercise intervention protocol for ethical reasons.

